### Sample size calculation

#### Pilot study phase

Because the judgements in this study phase will be mainly based on inter-rater reliability, we will calculate the sample size regarding this issue. According to [16], we will assume a difference between the overall agreement probability and the chance agreement probability of 0.3 and a relative error of 0.3. This will lead to a sample size of 123 subjects. For the pilot study phase, therefore, we expect there to be a duplicate diagnosis for 130 patients.

#### Feasibility study phase

The question of whether one of the two diagnostic procedures indicates for more or fewer patient-targeted referrals or therapies will be tested using a McNemar test.^3^ In a proportion of discordances in the one direction of 0.1 and in the other direction of 0.05 (i.e., 15% of the patients are discordant), and based on the conventional statistical assumptions (error of the first type < 0.05, power > 0.8), a difference between the two procedures can be statistically confirmed with 468 double-diagnosed patients. In the case of 20% discordant patients (with proportions of 0.13 vs. 0.07), 433 patients would be sufficient. For the feasibility study phase, therefore, we expect there to be a duplicate diagnosis for 500 patients.

### Data transfer to the University Department of Neurology (KNEU)

If the procedure described above is followed, the stored EEG data will initially only be available to the initiating physician. According to the protocol, an employee of KNEU will receive the two related EEGs and the assessment form on a data carrier (USB stick) in the practice of the neurologist. In the future, the safe medical network can be employed for this purpose.

### Randomized second assessment by KNEU

The Data Trustee of the KNEU will store the study EEGs and the assessments of the private practitioners separately from the clinic data. KNEU will first evaluate all EEGs according to the technical aspects. Patients with at least one EEG which cannot be assessed technically will not be included in the further method comparison.

Within the framework of the method comparison, KNEU will organize the conciliary second assessment (reference assessment) of the EEGs of each patient by two independent experts. For this purpose, the Data Trustee will pseudonymize the two EEGs of the same patients and randomly divide them before providing both of them to the two specialists who will independently judge them according to the standardized assessment form. After the re-identification of the EEGs by the Data Trustee, any discordance between the outcomes of the two second assessors will be ascertained and jointly (possibly with a mediator) decided whether different dispositions of the further case management result from the comparison of the two related EEGs from the point of view of the KNEU.

Subsequently, the findings of the KNEU will be compared with those of the private practitioner. For each patient, the private practitioner will receive conciliary feedback, in urgent cases by telephone (Fig. 1). A final concordance of the three physicians involved will not be required. The professional responsibility for patient management will remain with the practitioner.

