### Objectives of the *HOME* project and specific objectives of the HOME^ONE^ study

The goal of the *HOME* project is to implement an EEG home-monitoring system with a patient-controlled portable dry electrode EEG recorder for use within the routine care of outpatients (for diagnostic purposes as well as for therapeutic management). The HOME^ONE^ study will be a two-phase (pilot study phase and feasibility study phase) intra-individual comparison that is driven by the following aims:To evaluate the technical usability and efficacy of the new portable dry electrode EEG recorder in comparison to the conventional EEG devices (pilot study phase);

To determine whether the pilot study objectives are met, we will analyze the technical assessments and EEG record examinations of the private practitioners and two experienced neurologists (percent of concordant readings and kappa values). After the technical usability and efficacy are shown, the second HOME^ONE^ study phase will be conducted. This feasibility study will aim to:(2)Assess patients’ acceptability and the feasibility of the EEG home-monitoring (feasibility study phase);(3)Provide insights into the extent of expectable diagnostic and therapeutic yields (feasibility study phase).

To evaluate whether this feasibility study was successful, we will analyze the before and after documented diagnostic findings and the therapeutic consequences of the private practitioners and compare them with those of two experienced neurologists. As is the case in the pilot study phase, a technical assessment is also part of the analyses.

If the two phases of the HOME^ONE^ study provide sufficient justification for technical usability, practical feasibility, and diagnostic and therapeutic yields, this will justify (indication-specific) full-scale randomized controlled trials or observational studies.

To realize the goals of the *HOME* project (and the HOME^ONE^ study), which is being performed by the University Department of Neurology Magdeburg, we established a network of practices of neurologists in Saxony-Anhalt, a federal state of Germany.

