### Data analysis and measures

Comparing the two EEG recording methods, the conventional practice EEG cannot be the gold standard to determine the sensitivity, specificity, and predictive values of the portable EEG. The goal that underpins the use of the portable EEG is to gain additional diagnostic insights through extended use. However, in the present state of the method, the portable EEG can remain behind the conventional practice EEG in its diagnostic yield, for example, due to increased artifacts or errors in handling by the patient. As such, it will be necessary to document the technical assessment and the extent to which there is concordance between the two EEGs.

In the pilot study phase, all three assessors will evaluate the technical quality of the EEG records according to the following ratings:The EEG record is unrestrictedly for medical reporting,The use of the EEG record for medical reporting is limited, andThe EEG record is not usable for medical reporting.

The evaluation of the technical quality is based on different criteria:The assessor’s overall impression on the EEG record,The frequency of artifacts,Strength of 50 Hz line noise, andRecovery of EEG traces after strong artifacts.

These criteria meet the standards of the International Federation of Clinical Neurophysiology (IFCN) for digital recording of clinical EEG [15].

In addition, all three assessors will document their medical reports for each blinded EEG record. After re-identification of the EEGs and the associated medical reports by the Data Trustee, the concordance (or discordance) will be evaluated. As measurements, we will use concordance rates and kappa values.

In the feasibility study phase, we will use the same approach. However, we will extend it as follows: To share information regarding a possible change of management, the private practitioner will classify the results of the conventional practice EEG according to the possibilities presented in Table 1.

**Table 1 Tab1:** Action-oriented classification of the findings of the conventional practice EEGs

1A	No action or follow-up appointment only
1B	Targeted referral for further clarification or co-treatment or further treatment
1C	Initiate or change therapy (adjust, switch, settle)

In the same way, they will also classify the results of the portable EEG (see Table 2).

**Table 2 Tab2:** Action-oriented classification of the results of the portable EEG

2A	No action or follow-up appointment only

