2B	Targeted referral for further clarification or co-treatment or further treatment^a^
2C	Initiate or change therapy (adjust, switch, settle)

^a^If clarification or therapeutic clarity can only be established by targeted referral, this clarification is part of the contractual medical care, not the study

In a first simplified evaluation level, the combinations (1A and 2A) as well as ((1B or 1C) will be (2B or 2C)) concordant. This results in Table 3.

**Table 3 Tab3:** Test assessment of conventional and portable EEGs by the private practitioner

Practice EEG	Portable EEG		Total
	Action (2B, 2C)	No action (2A)	
Action (1B, 1C)	a	b	a + b
No action(1A)	c	d	c + d
Total	a + c	b + d	a + b + c + d

This represents an intra-individual method comparison with a binary result criterion (“change of management”): The case management sequences of the portable EEGs are the same as those of the conventional practice EEGs (a or d), they are beyond (c) or remain behind (b). No decision should be made at this level (c) being “better” than (b).

To develop patients’ acceptability, we will use a questionnaire to measure relevant factors.

In an extended evaluation level, the results of the portable EEG will be more differentiated by means of the possibilities shown in Table 4.

**Table 4 Tab4:** Differentiation possibilities of the portable EEG results in an extended evaluation level

2A	No action or follow-up appointment only
2B1	Referral to the same specialist as 1B
2B2	Referral to a specialist different than 1B
2C1	Same therapeutic decision as 1C
2C2	Other therapeutic decision than 1C

The combinations of 1A with 2A are concordant with 1B with 2B1 and 1C with 2C1. The other combinations are discordant. Since the expected number of discordances is higher than the previous simplified classification, more cases than stated above will be required.

In the second part of the documentation, the attending physicians will document their gain in case management through the additional portable EEG and determine their disposition for their patient. In doing so, they will decide for themselves which of the possibly discordant EEG findings they consider superior. Since they know both findings and the patient, their two EEG assessments are not independent of each other.

The result of the second opinion in KNEU is subsequently included for the method comparison.

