**Fig. 1 Fig1:**
[figure not shown]
Process sequence of data management, blinded second assessment (KNEU) and conciliary feedback to private practitioner

In the review of the EEG findings from the practice and the KNEU, there will be two four-fold tables (Table 5).

**Table 5 Tab5:** EEG assessments by the University Department of Neurology (KNEU) in relation to the previous assessment by the private practitioners

	Practice assessment		
Assessment KNEU	Action (2B, 2C)	No action(2A)	Total
Conventional practice EEG			
Action (1B, 1C)	a	b	a + b
No action (1A)	c	d	c + d
Total	a + c	b + d	a + b + c + d
Portable EEG			
Action (1B, 1C)	a	b	a + b
No action (1A)	c	d	c + d
Total	a + c	b + d	a + b + c + d

The first result criterion will be the proportion and the direction of the cases with discordant disposition of the two EEGs by the private practitioner (Table 3). The second criterion will be the proportion and direction of discordant results in the treatment regimen by specialists of KNEU within the framework of the pseudonymized second assessment.

In this way, it will be possible to determine how the KNEU physicians assess the portable EEG differently from the private practitioners in addition to generating insights into how these two physician groups differ from each other in terms of their assessments of the office-based EEG. Furthermore, it will be possible to observe how the assessments of the consulting physicians from KNEU differ from each other. These assessments will each be quantified as kappa values.

As a third result criterion and final evaluation level of method comparison, the original four-fold table will be prepared again after the consolidation of the first and second assessments (Table 6):

**Table 6 Tab6:** Consolidated EEG assessments jointly by the University Department of Neurology and by the private practitioners

Practice-EEG^a^	Portable EEG^b^		Total
	Action (2B, 2C)	No action(2A)	
Action (1B, 1C)	a	b	a + b
No action (1A)	c	d	c + d
Total	a + c	b + d	a + b + c + d

^a^
http://powerandsamplesize.com/Calculators/Compare-Paired-Proportions/McNemar-Z-test-2-Sided-Equality

^b^After consolidation of the initial assessment in practice and the second assessment in the University Department of Neurology

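### The method comparison keeps only patients with two readable EEGs, so it can favour the cap; the plan states no failure rate that its 500 patients allow for

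*Protocol article*

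**What the plan says.** The exclusion rule stands in the protocol article under Randomized second assessment by KNEU. After KNEU has checked all EEGs technically, "Patients with at least one EEG which cannot be assessed technically will not be included in the further method comparison". The rule applies whichever device failed.

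Under Data analysis and measures, the article expects that "the portable EEG can remain behind the conventional practice EEG in its diagnostic yield, for example, due to increased artifacts or errors in handling". The same section rates each recording on three technical grades, the lowest being unusable. It also defines the four cells of Table 3: the portable EEG leads to the same management (a or d), goes beyond the practice EEG (c), or falls behind it (b). There is no cell for an unreadable recording.

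Technical quality is also an outcome in the second phase. The objectives section says: "As is the case in the pilot study phase, a technical assessment is also part of the analyses".

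On size, the article plans to examine about 500 patients in the feasibility phase, and the sample size section concludes: "For the feasibility study phase, therefore, we expect there to be a duplicate diagnosis for 500 patients". The calculation asks for 468 double-diagnosed patients (discordance 0.10 versus 0.05) or 433 (0.13 versus 0.07). No failure or loss rate is given.

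**The concern.** The feasibility phase asks whether EEG recorded by patients at home changes management. In that phase the patient puts on and runs the cap without staff, so handling errors by the patient can arise only on the cap's side. If the practice EEG led to action and the cap recording is unreadable, the cap has fallen behind in the plainest sense. The rule takes that patient out of the comparison instead of placing the patient in cell b. The comparison is thus conditional on success of the device under test.

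The affected results are the second criterion (the KNEU assessment), the third (consolidated Table 6), and possibly the first (Table 3). The study is meant to justify full-scale trials partly on diagnostic and therapeutic yield. A yield estimated only where the cap worked may be too favourable for that use. Each exclusion also takes a pair from the McNemar test, and the plan does not say how many it can lose.

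**Working it through.** **1. Reproducing the planned size.** Inputs are the two discordance scenarios in the feasibility-phase calculation, "error of the first type < 0.05, power > 0.8", and a two-sided test, as shown by the calculator link printed under Table 6 ("McNemar-Z-test-2-Sided-Equality"). With s the sum and d the difference of the two discordant proportions:

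n = [1.960·√s + 0.8416·√(s − d²)]² / d²

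- 0.10/0.05: (0.7591 + 0.3232)² / 0.0025 = 468.6; the plan states 468.
- 0.13/0.07: (0.8765 + 0.3730)² / 0.0036 = 433.7; the plan states 433.

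Both figures reproduce.

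**2. Margin in 500.** (500 − 468)/500 = 6.4% in the first scenario and (500 − 433)/500 = 13.4% in the second.

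**3. Power if a fraction f of 500 patients is excluded.** Power = Φ[(d√n − 1.960·√s) / √(s − d²)], with n = 500(1 − f). The values of f are assumptions.

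| f | n | 0.10/0.05 | 0.13/0.07 |
|---|---|---|---|
| 0 | 500 | 82.5% | 85.3% |
| 5% | 475 | 80.5% | 83.5% |
| 10% | 450 | 78.4% | 81.4% |
| 20% | 400 | 73.5% | 76.7% |
| 30% | 350 | 67.7% | 71.1% |

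**4. How far the comparison could shift.** The article gives neither a failure rate nor the proportion q of practice EEGs that lead to action. Assume:

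- c = 0.10 and b = 0.05 among usable pairs;
- every failure is the cap's;
- failures are unrelated to the practice finding;
- a failed cap recording counts as no action.

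Then c = 0.10(1 − f) and b = 0.05(1 − f) + f·q, so c − b = 0.05(1 − f) − f·q. With failures excluded, c − b stays at 0.050.

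- q = 40%: 0.0275 at f = 5%; 0.045 − 0.040 = 0.005 at f = 10%; 0.040 − 0.080 = −0.040 at f = 20%.
- f = 10%: 0.025 with q = 20% and −0.015 with q = 60%.
- The difference is zero at f = 0.05/(0.05 + q), which is 14.3%, 11.1% and 9.1% for q = 30%, 40% and 50%.

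**5. Two checks on that model.** The article does not say which direction carries the 0.10. If it is b, then c − b = −0.05(1 − f) − f·q. At f = 10% and q = 40% this is −0.085, against −0.050 with failures excluded, so the exclusion again favours the cap. Conventional failures work the other way. If a fraction g of practice EEGs fails and the cap leads to action in a proportion r of those patients, c gains g·r. The net effect therefore depends on f·q against g·r, and the documents give none of the four.

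**The case against.** Several stronger readings are tempting, and the documents do not support them.

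- **That the cap's failures disappear from the study.** They do not. All recordings are rated technically before any exclusion, and this is analysed in both phases. What is lost is the link: a failure rate alone does not show how many failures cost the patient a management action.
- **That the rule removes exactly the patients in whom the cap lags.** It removes only recordings that cannot be assessed. Those graded as limited stay in and can still fall into cell b. Conventional failures are removed as well.
- **That Table 3 is certainly filtered.** The rule stands in the KNEU section and speaks of the further comparison, while the practitioner's assessment is made before KNEU receives the data. On the other hand, the article calls Table 3 an intra-individual method comparison and Table 6 the last level of method comparison. The scope is open.
- **That the planned size assumes no failures.** The text equates about 500 examined with 500 double-diagnosed patients, but only 468 or 433 are needed. At 10% exclusions the second scenario still has 81.4% power, and the first is 1.6 points below 80%.
- **That the result would reverse.** The reversal in the illustration rests on an assumed failure rate, action rate and direction. The test is two-sided, and the article declines at this level to call c better than b.

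It is also fair that this is a feasibility phase, begun only after technical usability has been shown in the pilot. These points narrow the concern, but the conditioning on readable recordings remains.

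**Conclusion.** The concern holds in a limited form. At least the KNEU assessment and the consolidated table, and possibly Table 3, describe only patients in whom both recordings could be read. Since the article itself expects the cap to lag through artifacts and handling errors, the management comparison can favour the cap. Separate technical ratings do not correct this.

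The size cannot be fixed from the documents. Under the assumptions in step 4, with a 40% practice action rate, a 5-point difference shrinks to 0.5 points at 10% cap failures and vanishes at 11.1%. These figures show sensitivity and are not a forecast.

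The effect on power is secondary. It matters above 6.4% exclusions in the 0.10/0.05 scenario and above 13.4% in the 0.13/0.07 scenario, and it is modest at 10%.

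**What to change.** 1. State whether the exclusion applies to Table 3 or only to the KNEU and consolidated tables.
2. Add an analysis of all patients in whom both EEGs were attempted. Cross-classify action, no action and unusable for each device. Run a McNemar analysis of action derived versus not derived, in which an unusable recording from either device counts as not derived. Keep concordance and kappa on usable pairs: if failures were coded as no action there, each cap failure paired with a no-action practice EEG would count as agreement (60% of them at a 40% action rate). Report both sets of results.
3. Report the unusable proportion per device with a 95% confidence interval, over all patients examined.
4. State that 500 examined patients keep 80% power only up to about 6.4% exclusions for 0.10/0.05 (13.4% for 0.13/0.07), with about 78%, 73% and 68% at 10%, 20% and 30% exclusions for 0.10/0.05. These figures belong to the usable-pair test; the added analysis will have other discordance proportions.

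The cost is some extra analysis on ratings that are already collected, and a result that may be less favourable to the cap.

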**Fig. 1 Fig1:**
[figure not shown]
Process sequence of data management, blinded second assessment (KNEU) and conciliary feedback to private practitioner

In the review of the EEG findings from the practice and the KNEU, there will be two four-fold tables (Table 5).

**Table 5 Tab5:** EEG assessments by the University Department of Neurology (KNEU) in relation to the previous assessment by the private practitioners

	Practice assessment		
Assessment KNEU	Action (2B, 2C)	No action(2A)	Total
Conventional practice EEG			
Action (1B, 1C)	a	b	a + b
No action (1A)	c	d	c + d
Total	a + c	b + d	a + b + c + d
Portable EEG			
Action (1B, 1C)	a	b	a + b
No action (1A)	c	d	c + d
Total	a + c	b + d	a + b + c + d

The first result criterion will be the proportion and the direction of the cases with discordant disposition of the two EEGs by the private practitioner (Table 3). The second criterion will be the proportion and direction of discordant results in the treatment regimen by specialists of KNEU within the framework of the pseudonymized second assessment.

In this way, it will be possible to determine how the KNEU physicians assess the portable EEG differently from the private practitioners in addition to generating insights into how these two physician groups differ from each other in terms of their assessments of the office-based EEG. Furthermore, it will be possible to observe how the assessments of the consulting physicians from KNEU differ from each other. These assessments will each be quantified as kappa values.

As a third result criterion and final evaluation level of method comparison, the original four-fold table will be prepared again after the consolidation of the first and second assessments (Table 6):

**Table 6 Tab6:** Consolidated EEG assessments jointly by the University Department of Neurology and by the private practitioners

Practice-EEG^a^	Portable EEG^b^		Total
	Action (2B, 2C)	No action(2A)	
Action (1B, 1C)	a	b	a + b
No action (1A)	c	d	c + d
Total	a + c	b + d	a + b + c + d

^a^
http://powerandsamplesize.com/Calculators/Compare-Paired-Proportions/McNemar-Z-test-2-Sided-Equality

^b^After consolidation of the initial assessment in practice and the second assessment in the University Department of Neurology

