**Methods:**

The HOME^ONE^ study is the first step in the process of investigating whether outpatient EEG home-monitoring changes the diagnosis and treatment of patients in comparison to conventional EEG (“change of management”). Both EEG devices (conventional and portable) will be systematically compared via a two-phase intra-individual assessment.

In the first phase (pilot study phase), both EEG devices will be used within neurologist practices (all other things being equal). This pilot study (involving 130 patients) will evaluate the technical usability and efficacy of the new portable dry electrode EEG recorder in comparison to conventional EEG devices. Judgements will be based on technical assessments and EEG record examinations of private practitioners and two experienced neurologists (percent of concordant readings and kappa values).

The second phase (feasibility study phase) aims to assess patients’ acceptability and feasibility of the EEG home-monitoring and will provide insights into the extent diagnostic and therapeutic yields can be expected.

For this purpose, a conventional EEG will be recorded in neurologist practices. Thereafter, the practice staff will instruct the patients on how the portable EEG device functions. The patients will subsequently use the devices in their home environment.

The evaluation will compare the before and after documented diagnostic findings and the therapeutic consequences of the private practitioners with those of two experienced neurologists.

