## Background

At present, EEGs can only be recorded with considerable effort over a prolonged period of time under the everyday conditions of the patient. Patients are also unable to place an EEG cap on their own. To address these issues, a portable dry electrode EEG recorder (Fourier One) was developed. This new EEG device, which is integrated into a patient-friendly cap, records brain waves continuously or patient-controlled over a longer period of time. The patient can place the portable EEG device independently without the help of medical staff. With the development of this new EEG device, it is also possible to record brain waves outside medical facilities over a period of time ranging from several hours through to days under everyday conditions in the patient’s home. This results in new possibilities for the differential diagnosis of suspected cases of epilepsy, unclear consciousness disturbances, sleep disturbances, ADHD, or other disorders of the CNS, in contrast to other causes. The use of the new EEG device might also result in changes in the therapeutic management (e.g., changes in medication). These possible changes are summarized under the term “change-of-management” and reflect the therapeutic yield of a patient-controlled EEG home-monitoring. In this regard, the new portable dry electrode EEG recorder is intended to be used for both diagnostic performance and part of the therapeutic management.

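### All three named result criteria compare one EEG with the other; the practitioner's disposition after both EEGs, which is where a change of management would show, enters none of them

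*Protocol article*

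**What the plan says.** **The question.** The abstract of the protocol article describes the study as "investigating whether outpatient EEG home-monitoring changes the diagnosis and treatment of patients in comparison to conventional EEG". The Background, after mentioning changes in therapeutic management such as medication, adds: "These possible changes are summarized under the term “change-of-management” and reflect the therapeutic yield of a patient-controlled EEG home-monitoring". The Objectives section says that, to judge the feasibility phase, "we will analyze the before and after documented diagnostic findings and the therapeutic consequences of the private practitioners", with the two second readers as comparators. Objective (3) is to give insight into the extent of diagnostic and therapeutic yield that can be expected.

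**The measure.** In Data analysis and measures, the practitioner gives the conventional EEG a code (1A no action, 1B referral, 1C therapy) and the portable EEG a code on the same scale (2A, 2B, 2C). Table 3 crosses the two, with B and C merged into action. The article says of it: "This represents an intra-individual method comparison with a binary result criterion (“change of management").

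**The disposition.** The same section then describes a second part of the documentation, in which "the attending physicians will document their gain in case management through the additional portable EEG and determine their disposition for their patient". Where the two EEGs conflict, the physician chooses which one to follow.

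**The criteria.** Randomized second assessment by KNEU (the university department) names three:
- First, from Table 3: "The first result criterion will be the proportion and the direction of the cases with discordant disposition of the two EEGs by the private practitioner".
- Second: the proportion and direction of discordance in the department's pseudonymized second assessment.
- Third: the four-fold table of practice EEG against portable EEG, prepared again after the first and second assessments are consolidated (Table 6).

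**The concern.** In the feasibility phase the portable EEG is added to a conventional EEG that has already been recorded. The yield question is therefore whether the plan after both EEGs differs from the plan on the conventional EEG alone. Table 3 asks something else: whether the two recordings, each given its own action code, point the same way. The article nevertheless gives Table 3 the change-of-management label.

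The two quantities differ in both directions. A patient in cell b (conventional action, portable no action) may keep the action, and a patient in cell c (conventional no action, portable action) may have the portable finding set aside. In both cases management is unchanged, yet the patient is counted as discordant. Conversely, a patient coded 1B and 2C sits in concordant cell a, although a referral may have become a change of therapy.

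At stake is the reading of the result for objective (3). A discordance rate reported under the change-of-management label could be taken as the share of patients whose care changed.

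**Working it through.** **1. What the sample size covers.** The inputs are in Sample size calculation, Feasibility study phase: discordant proportions 0.10 and 0.05 (second scenario 0.13 and 0.07), type I error 0.05, power 0.80. The calculator link in the Table 6 footnote points to the two-sided McNemar Z-test. With s the sum and d the difference of the two proportions:

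n = [1.960·√s + 0.842·√(s − d²)]² / d²

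- 0.10 and 0.05: s = 0.15, d = 0.05, n = 468.6 (stated 468).
- 0.13 and 0.07: s = 0.20, d = 0.06, n = 433.7 (stated 433).

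The stated figures reproduce. The quantity they size is the difference between cells b and c of Table 3, a comparison of two recordings.

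**2. What Table 3 says about changed management.** Let fc and fb be the shares of cells c and b in which the final disposition follows the portable EEG. The article gives neither, so each is allowed to run from 0 to 1. Among discordant patients, the proportion who move between action and no action is

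c·fc + b·fb.

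For N = 500, scenario 1 has 500 × 0.10 = 50 and 500 × 0.05 = 25 discordant patients, 75 in all. The article does not say which direction has which proportion.

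| Assumption | Patients changed, of 500 |
|---|---|
| fc = fb = 0 | 0 (0%) |
| fc = 1, fb = 0, c = 0.10 | 50 (10%) |
| fc = 1, fb = 0, c = 0.05 | 25 (5%) |
| fc = fb = 0.5 | 37.5 (7.5%) |
| fc = fb = 1 | 75 (15%) |

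In scenario 2, 500 × (0.13 + 0.07) = 100, so the range is 0 to 100 (0% to 20%). Within a scenario, for a given assignment of the two proportions to cells b and c, every row is compatible with the same Table 3.

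**3. What lies outside the discordant cells.** At the simplified level every combination of 1B or 1C with 2B or 2C is concordant. A change from class B to class C therefore falls in cell a and adds to the figures above. The article gives no size for cell a or for changes within it, so no upper limit for the total can be computed.

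**4. Whether the other two criteria close the gap.** The second criterion is the department's view, while responsibility for management stays with the practitioner. The third merges the assessors but still leaves one class per EEG. Neither is the practitioner's documented disposition.

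**The case against.** Several points on the other side have force.

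- **A before/after analysis is promised.** The Objectives section says so, and the Discussion intends to use recorded follow-up dispositions for a cost comparison. A reader might infer that change of management goes unanalysed; the article does not support that. What remains is that none of the named criteria carries out the promised analysis, while one of them bears its label.
- **The second criterion is more than a cross-table.** After re-identification the department jointly decides whether the two related EEGs lead to different case management. That is a judgement with both EEGs in view, but not by the physician who decides.
- **The practitioner's codes are not isolated readings.** The article says the two assessments are not independent, so the portable code may partly anticipate the decision. The article still lists the disposition as a separate item.
- **Table 4 is finer.** The extended level separates same from different referrals and therapies, and treats 1B with 2C as discordant. It still codes the portable result against the conventional one, and the first and third criteria use the simplified table.
- **McNemar hides nothing.** A reader might infer that equal discordance in both directions would conceal changed management. The first criterion reports proportion as well as direction, and the test is assigned only to whether one procedure leads to more or fewer referrals or therapies. A null answer to that question would be correct.

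**Conclusion.** The point holds as one of labelling and of a missing named criterion. Table 3 discordance is not the change-of-management rate, and the recorded disposition that could supply that rate is used in none of the three criteria. Under the article's 0.10 and 0.05 with N = 500, change between action and no action among the 75 discordant patients can be anything from 0 to 75. This is a bound that rests on unstated adoption shares, not a prediction, and changes within cell a are additional.

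Two further readings are tempting and not supported. One is that the true rate must lie below raw discordance: changes within cell a can push it above, so the direction of the error is unknown. The other is that the move to full-scale trials depends on this figure: the Objectives section rests that step on technical usability, practical feasibility, and diagnostic and therapeutic yields together.

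The sample size arithmetic is sound for the comparison it addresses.

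**What to change.** For objective (3), add a named result criterion that crosses the disposition on the conventional EEG alone (1A, 1B, 1C) with the practitioner's documented disposition after both EEGs. Report the proportion of patients whose class changed, with a confidence interval, and by direction. Keep Tables 3 and 6 and the McNemar test as the method comparison, without the change-of-management label.

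Precision would be adequate at the planned size. If, for illustration, 50 of 500 changed, the 95% half-width is 1.96 × √(0.10 × 0.90 / 500) = 2.6 percentage points, ignoring clustering by practice.

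Cost: no extra patients or procedures, and one more cross-table. Two details need settling:
- The article does not say that the final disposition is coded in classes A, B and C, so one form field or a coding rule may be needed.
- The cross is a true before/after comparison only if the 1A–1C code is entered before the portable EEG is read. The article describes the practitioner examining both EEGs after the headset is returned and does not state when this code is fixed, so the form should state the order.
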